### Outcomes

The study's primary outcome is the lowest MAP recorded within the first 10 minutes following the induction for intubation.

Secondary outcomes include:

–Average MAP within the first hour after induction.–Mortality within the first hour after induction.–Cardiac arrest within the first hour after induction.–Occurrence of severe hypotension, defined as systolic blood pressure (SBP) < 80mmHg, within 1 hour after induction.–Occurrence of severe hypoxemia, defined as peripheral oxygen saturation (SpO_2_) < 85%, within one hour after induction.–Time for successful intubation.

Tertiary outcomes include:

–The number of intubation attempts.–The highest HR within 1 hour after induction.–The total dose of vasopressors administered within the first 24 hours, using the noradrenaline equivalent dose.–Mean change in vasopressor dose (norepinephrine equivalent) from baseline to hour 1.–Ventilator-free days within the first 7 days, defined as the number of days on which individuals are able to breathe spontaneously without any invasive ventilatory assistance, ascribing zero days to those who die within 7 days.–Mortality at day 7.–ICU mortality.–Hospital mortality.

Safety outcomes will be assessed during the first 10 minutes following induction, and will include:

–Hypertension, defined as SBP > 180mmHg.–Laryngospasm, as reported by the physician in charge of intubation.–Bradycardia, defined as HR < 45 bpm.–Arrhythmias.–Bronchoaspiration, defined as the presence of gastric content aspirated into the airway during intubation.

All outcome data will be presented as specified on the electronic supplemental materials (Table 1S - Supplementary Material). The trial sequence is available in figure 1.

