### Data collection

Demographic characteristics, comorbidities, clinical data, and severity of illness will be collected at baseline for all patients (Table 2S - Supplementary Material). Additional data on the procedure characteristics will also be collected (Table 3S - Supplementary Material). During and after the procedure, hemodynamic data will be registered at the following time points: 1 minute before induction; every 2 minutes during the first 10 minutes after the administration of the study medication; every 5 minutes up to one hour after induction (Table 4S - Supplementary Material). Doses of vasoactive drugs will also be recorded. Any adverse events occurring within the first hour post-induction, including death, cardiac arrest, arrhythmias, bronchoaspiration, and laryngospasm, will be documented.

Patients will be followed until hospital discharge, censored at day 60^th^, to determine the need for mechanical ventilation up to day 7, vital status at day 7, in the ICU, and in the hospital. Patients who are withdrawn from the study for safety reasons (excluding those who withdraw consent) will be included in the analysis on an intention-to-treat basis.

Data will be collected via electronic forms using the RedCap platform and securely stored. The investigators will complete the forms, using specific passwords for access. Training will be provided for all personnel involved in the study to ensure high-quality data collection. The principal investigator will be available to answer any questions regarding form completion. Data consistency will be periodically reviewed, and any discrepancies will be addressed by contacting the sites for clarification and correction.

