### Statistics

#### Sample size calculation and interim analysis

We plan to randomize an adequate number of patients to ensure 170 patients who are successfully intubated and consented to participate. Based on the assumption that some patients may be randomized but not intubated, or consent could not be obtained, we anticipate that more than 170 patients will need to be randomized. This sample size will provide 90% power with an alpha of 0.05 to detect a 10mmHg difference in the lowest MAP within the first 10 minutes after induction for intubation, assuming a standard deviation of 20mmHg. The study steering committee determined the minimum clinically important difference of 10mmHg.

An interim analysis will be performed after the inclusion of 80 patients to assess the safety profile of the intervention concerning the primary outcome. The study will not be terminated for benefit or futility unless a safety threshold of p < 0.01 is reached, particularly if significant differences in MAP favor the propofol group. This analysis will be conducted by an independent external DSMB, which will remain unblinded to group allocation. The DSMB will also review adverse events and the safety profile to provide recommendations.

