#### Statistical analysis

Our primary analysis will follow a modified intention-to-treat (mITT) approach. As clinical management might change after randomization, we expect that some patients who will be randomized will not be intubated. Similarly, as we will use a deferred (opt-out) consent process, some patients (or representatives) might not consent. Thus, our mITT analysis will include only those patients who will be intubated and who consent to participate. The data analysis will be performed after submitting the protocol paper and analysis plan for publication.

Categorical variables will be expressed as counts and percentages. Continuous variables will be presented as means and standard deviations (SD) or medians with interquartile ranges (IQR, 25th -75th percentile) as appropriate. For all outcomes, including the primary outcome, we will not impute missing data, and the number of missing values will be clearly presented in tables. Treatment adherence will be reported as each group's mean (SD) number of successful medication administrations.

The primary outcome (lowest MAP within the first 10 minutes post-induction) will be analyzed using a linear regression model, adjusted for baseline MAP before induction, total vasopressor dose in the first 10 minutes, age, and a random patient intercept. A MAP value of 10mmHg (the average cardiovascular filling pressure) will be considered in patients with cardiac arrest.^(14)^ Other vasopressors will be converted to noradrenaline dose equivalents. A per-protocol analysis will be performed, including only patients who received the assigned medication. Additionally, we conducted sensitivity analysis considering the lowest measured blood pressure before cardiac arrest and an unadjusted analysis. In all primary outcome analyses, the effect estimate will be expressed by the mean difference with 95% confidence intervals (95%CI) and p values reported.

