For secondary binary and exploratory outcomes, logistic regression will be used, with the effect estimate expressed as odds ratios (ORs) and 95%CIs, with their respective p values. Deaths within the specified ranges will be considered zero free days for outcomes related to free days (ventilator-free days in 7 days). Logistic regression models for ordinal data will report proportional ORs. The frequency of adverse events will be expressed as counts and percentages, and comparisons will be made using the Chi-squared test for categorical variables. Secondary outcomes will not be adjusted for covariates.

For the primary outcome, a pre-specified subgroup analysis will evaluate the following groups: patients < 70 *versus* ≥ 70 years old; patients with a Sequential Organ Failure Assessment (SOFA) score < 8 *versus* ≥ 8 points; patients on vasopressor *versus* without vasopressors; and patients with acute respiratory distress syndrome (ARDS) *versus* those without ARDS. Each subgroup analysis will be performed using linear regression, adjusted for baseline MAP before induction, total vasopressor dose in the first 10 minutes, age, and a random patient intercept. Effect estimates will be reported as mean differences with 95%CIs for each subgroup, with respective interaction p values. We will not adjust for multiplicity.

We will consider a significant two-tailed p level ≤ 0.05. Analysis will be performed using R software in the available version (R Foundation for Statistical Computing), Vienna, Austria.

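### The no-adjustment rule for secondary outcomes also covers average first-hour MAP, so that comparison is less precise than the collected data allow

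*Protocol article*

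**What the plan says.** The Outcomes section of the Protocol article lists "Average MAP within the first hour after induction" among the secondary outcomes. The Statistical analysis section then says of secondary outcomes as a class: "Secondary outcomes will not be adjusted for covariates". The sentences around this rule deal with binary, ordinal and adverse-event outcomes, but the rule is not limited to them.

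The primary outcome, the lowest MAP in the 10 minutes after induction, is handled differently. Its linear model is "adjusted for baseline MAP before induction, total vasopressor dose in the first 10 minutes, age, and a random patient intercept".

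The Data collection section shows that the baseline value exists: "hemodynamic data will be registered at the following time points: 1 minute before induction". Later readings are scheduled "every 2 minutes during the first 10 minutes after the administration of the study medication; every 5 minutes up to one hour after induction". The article does not say whether the first-hour average is a simple mean of these readings or is weighted by time.

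The Randomization and concealment section stratifies by study site and vasopressor use.

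**The concern.** The plan has two post-induction MAP outcomes and one pre-induction MAP reading. It uses that reading for the first outcome and rules it out for the second, without giving a reason. A pre-treatment measurement of the same quantity is usually the most useful covariate for a continuous outcome. Leaving it out leaves explainable between-patient variation in the error term and widens the confidence interval. The blanket rule also excludes the two stratification factors.

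Because the rule is explicit, a later analysis plan could not add the adjustment without contradicting the published protocol. If adjustment were added after the results were seen, it would look chosen for its effect.

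A second matter is the reading schedule, which is denser in the first 10 minutes than later. If the average is taken as a plain mean of readings, that period counts for more than its share of the hour.

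**Working it through.** **Inputs from the Protocol article.** 170 analyzed patients, allocated 1:1, so 85 per arm. Two-sided alpha 0.05, power 90%, difference 10 mmHg and SD 20 mmHg, the last two stated for the lowest MAP only. Reading times are as quoted above.

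**Assumptions.** The correlation r between baseline and first-hour average MAP is not given, so a range of 0.3, 0.5 and 0.6 is shown. For results in mmHg, the SD of 20 is borrowed for the first-hour average. The percentages do not depend on that SD.

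**Step 1: the plan's own figure.** n per arm = 2 × (1.960 + 1.282)² × (20/10)² = 84.1, rounded up to 85, or 170 in total. Power at 85 per arm is 90.3% by the normal approximation and 90.0% by the noncentral t. The stated sample size reproduces and is not in question.

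**Step 2: precision with and without baseline MAP.** Unadjusted SE = 20 × √(2/85) = 3.07 mmHg, so the 95% CI half-width is 1.96 × 3.07 = 6.0 mmHg. Adjusting for baseline multiplies the SE by √(1 − r²). The equivalent gain in sample size is 1/(1 − r²) − 1.

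| r (assumed) | √(1 − r²) | SE reduction | Equivalent extra patients | 95% CI half-width, mmHg |
|---|---|---|---|---|
| 0 | 1.000 | 0% | 0% | 6.0 |
| 0.3 | 0.954 | 5% | 10% | 5.7 |
| 0.5 | 0.866 | 13% | 33% | 5.2 |
| 0.6 | 0.800 | 20% | 56% | 4.8 |

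These figures are for baseline MAP alone. Any gain from site and vasopressor use is not quantified.

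**Step 3: weighting, only if a simple mean is used.** Readings at 2, 4, 6, 8 and 10 minutes make 5; readings from 15 to 60 minutes in steps of 5 make 10. The first 10 minutes then hold 5/15 = 33.3% of the weight for 10/60 = 16.7% of the hour. A trapezoidal time-weighted mean from minute 2 to minute 60 puts 10.5/58 = 18.1% on the same five readings.

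The consequence depends on the shape of the treatment difference over the hour:

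- 10 mmHg in the first 10 minutes and none afterwards: 10 × 5/15 = 3.3 mmHg in the simple mean, against 10 × 10/60 = 1.7 mmHg weighted by time.
- 10 mmHg early and 5 mmHg afterwards: (10 × 5 + 5 × 10)/15 = 6.7 mmHg, against (10 × 10 + 5 × 50)/60 = 5.8 mmHg.
- A constant difference: the same result either way.

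**The case against.** The strongest reply is that a prespecified unadjusted analysis of a secondary outcome is a legitimate choice. Under randomization it is unbiased, and its standard error already allows for chance imbalance in baseline MAP. This stands. A reader might infer that omitting baseline MAP biases the result, but the documents do not support that; the loss is of precision only.

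The size of the loss rests on a correlation that the article does not give. Vasoactive drugs may be started before induction and adjusted during the procedure, which could weaken the link between baseline and later MAP. At r = 0.3 the gain is only 5% of the SE. This also stands, and it is why a range is shown. Average MAP is one of several unranked secondary outcomes and carries no power claim, so it should not be called the main one.

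On weighting, a reader might infer that the plan does give the first 10 minutes double weight and so doubles an early effect. The documents do not support this. The averaging rule is not stated in the article and may be in the analysis plan or the supplement. Even with a simple mean, two thirds of the readings fall after minute 10. A factor of two arises only if the difference is confined to the first 10 minutes. Nor would a simple mean largely repeat the primary outcome, which is a minimum rather than a mean. Both arms share the schedule, so the comparison stays valid; what changes is the quantity being estimated.

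None of this answers the main point. The no-adjustment rule is explicit, it covers this outcome, and the baseline value is already collected.

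**Conclusion.** The concern holds as a matter of efficiency. The rule gives up precision for average first-hour MAP that the trial's own data could supply: about 5%, 13% or 20% of the SE at assumed correlations of 0.3, 0.5 or 0.6. The direction is secure whenever baseline and first-hour MAP are appreciably correlated; the size is not known from the documents. Validity, the primary analysis and the sample size are untouched.

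The weighting point is subsidiary and applies only if a simple mean of the scheduled readings is used.

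**What to change.** In the Statistical analysis section, exempt average first-hour MAP from the no-adjustment sentence and leave the rule in place for the other secondary outcomes. Analyze this outcome by linear regression adjusted for baseline MAP, site and vasopressor use as recorded at randomization. Report the mean difference with its 95% CI, and keep the unadjusted comparison as a sensitivity analysis.

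State how the average is formed. If a simple mean was intended, a time-weighted average (area under the MAP-time curve divided by the length of the hour) would describe the hour better. Dividing only by the time observed is not enough, because patients who die or arrest within the hour would then be represented by their pressures before the event alone. Handle them consistently with the primary outcome, which assigns a fixed MAP value after cardiac arrest and has a sensitivity analysis based on the lowest pressure measured before it.

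The cost is a few sentences and a few lines of code, with no new data. The change should be made and dated before the outcome data are analyzed.

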### Safety and adverse events

Given the severely ill ICU population undergoing intubation, we anticipate potential complications. These events will only be considered adverse if they are potentially related to the study treatment or deemed unexpected by the attending physician and unrelated to the underlying critical illness that led to intubation. (Table 5S - Supplementary Material)

Serious adverse events will be those that are life-threatening, result in death, lead to prolonged hospitalization, or cause severe and permanent disability. They will be adjudicated by physicians independent from the study team and reported to the DSMB and ethics committees.

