### Blinding

Blinding of healthcare professionals is not feasible due to the distinct visual differences between propofol (a white lipid emulsion) and ketamine (colorless). However, data collectors, outcome assessors, and statisticians will remain blinded to group allocation to minimize bias.

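### The adverse-event definition depends on attribution judgements in an open-label trial, and the text allows counts filtered in this way to be tested between arms

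*Protocol article*

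**What the plan says.** Five parts of the protocol article bear on this.

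- **Safety and adverse events.** The counting rule is: "These events will only be considered adverse if they are potentially related to the study treatment or deemed unexpected by the attending physician". The sentence goes on to require that the event be "unrelated to the underlying critical illness that led to intubation". Serious events are adjudicated by physicians outside the study team.
- **Data collection.** "Any adverse events occurring within the first hour post-induction, including death, cardiac arrest, arrhythmias, bronchoaspiration, and laryngospasm, will be documented".
- **Statistical analysis.** "The frequency of adverse events will be expressed as counts and percentages, and comparisons will be made using the Chi-squared test for categorical variables".
- **Blinding.** Treating staff cannot be blinded because the two drugs look different. The protection offered is that "data collectors, outcome assessors, and statisticians will remain blinded to group allocation to minimize bias".
- **Outcomes.** "Safety outcomes will be assessed during the first 10 minutes following induction". The list is hypertension and bradycardia (each with a numerical threshold), laryngospasm (reported by the intubating physician), arrhythmias and bronchoaspiration. No attribution condition is attached to any of them. Severe hypotension, severe hypoxemia, cardiac arrest and death within 1 hour are separate secondary outcomes.

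**The concern.** A between-arm comparison of event counts is protected by randomisation only if an event is counted in the same way in both arms. Here, whether a complication counts depends on someone's view of its cause or expectedness, and at least one of the people judging knows the drug. The Introduction describes propofol as tending to lower blood pressure and ketamine as a cardiovascular stimulant, and it hypothesises fewer complications with ketamine. A clinician who shares those expectations could attribute the same arrhythmia differently in the two arms. Blinded data collectors and assessors do not cure this if the judgement is made before the event reaches them.

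The comparison would then partly measure attribution rather than event rate. This could create a difference that does not exist or hide one that does. The counts matter to the conclusions: the Discussion says that propofol could remain an option if it had fewer adverse events.

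**Working it through.** **1. The plan's own figure.** The document gives no figure for the adverse-event comparison. Its sample size fixes the arm size used below. With difference 10 mmHg, SD 20 mmHg, two-sided alpha 0.05 and power 90%:

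n per arm = 2 × (1.960 + 1.282)² × 20² / 10² ≈ 84.1, rounded up to 85, so 170 in total. This reproduces the stated 170 (power 0.903 by the normal approximation, 0.900 by noncentral t).

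**2. The sections side by side.**

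| Event | Where it appears | Attribution filter stated there? |
|---|---|---|
| Lowest MAP | Primary outcome, 10 minutes | No |
| Severe hypotension, severe hypoxemia, cardiac arrest, death | Secondary outcomes, 1 hour | No |
| Hypertension, bradycardia | Safety outcomes, 10 minutes, numerical thresholds | No |
| Arrhythmias, laryngospasm, bronchoaspiration | Safety outcomes, 10 minutes; also named as adverse events to 1 hour under Data collection | Not under Outcomes; yes if the adverse-event definition governs |
| Any other complication | Adverse events only | Yes |

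The last two rows are where the definition can decide what enters the chi-squared test. For the three named events, the text does not settle which rule applies.

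**3. What unequal attribution would do (illustration).** Inputs: 85 per arm, from the plan. The true event rates and the share of events that pass the filter in each arm are assumptions.

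*Single tables, with 40 of 85 patients per arm having an event and no true difference:*

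- 70% v 40% counted: 28 v 16, or 33% v 19%. Odds ratio = (28 × 69) / (57 × 16) = 2.12. Pooled proportion 44/170 = 0.259; z = 0.141 / √(0.259 × 0.741 × 2/85) = 2.10; uncorrected p = 0.036. With a continuity correction, p is about 0.054.
- 60% v 40% counted: 24 v 16. Odds ratio = (24 × 69) / (61 × 16) = 1.70. z = 0.094 / √(0.235 × 0.765 × 2/85) = 1.45; uncorrected p = 0.15.

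*Probability of a significant result when true rates are equal.* This is an exact binomial enumeration of the uncorrected two-sided 5% chi-squared test. The apparent odds ratio is in brackets.

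| True rate, both arms | All counted | 50% v 50% | 60% v 40% | 70% v 40% |
|---|---|---|---|---|
| 20% | 0.052 | 0.050 | 0.138 (1.57) | 0.238 (1.87) |
| 30% | 0.050 | 0.050 | 0.193 (1.61) | 0.355 (1.95) |
| 40% | 0.050 | 0.052 | 0.261 (1.66) | 0.481 (2.04) |
| 50% | 0.055 | 0.051 | 0.328 (1.71) | 0.598 (2.15) |

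A filter that works equally in both arms leaves the error rate intact. Only unequal filtering inflates it.

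*A real difference can be hidden.* With true rates 40% v 20%, power is 0.82 if all events are counted. An equal 50% filter gives 20% v 10% counted and power 0.45. If 40% v 70% of events are counted, the counted rates are 0.40 × 0.40 = 16% v 0.20 × 0.70 = 14%, and the rejection probability is 0.06.

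**The case against.** The strongest reply is that the definition may never touch the tested counts. The chi-squared sentence is the only one that plausibly gives a method for the listed safety outcomes, and its term for adverse events may simply mean that unfiltered list. If Data collection uses the term without a filter, Statistical analysis may do so too. The definition also refers to a supplementary table that is not shown and may list the events. This stands as far as it goes: the document is ambiguous and does not prove that filtered counts will be tested. But the only definition printed is the attribution-based one, and a team that follows it would test filtered counts.

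Four stronger readings are tempting, and the document does not support them.

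- *That physicians' beliefs about hypotension would distort the results through this rule.* Lowest MAP and severe hypotension are measured outcomes that do not pass through the definition. The same holds for severe hypoxemia, and death and cardiac arrest also have their own unfiltered 1-hour outcomes.
- *That the attending physician makes every judgement.* Grammatically, that role is attached only to expectedness. Who judges relatedness is not stated.
- *That the DSMB sees only filtered counts.* The document says that it reviews adverse events and the safety profile, and does not say how they are counted.
- *That serious events reach independent adjudication only after the filter.* No such order is given.

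It is also fair to say that possible relatedness is a low bar, that bronchoaspiration is defined as occurring during intubation, and that every rate in the illustration is assumed. Among the named events, the part with no unfiltered outcome is therefore mainly arrhythmia between 10 minutes and 1 hour. The remaining exposure is to unlisted complications, and to all three named events if the definition governs them.

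**Conclusion.** The point holds in a limited form. As printed, the definition makes counting depend on relatedness, expectedness and the role of the underlying illness; the attending physician is not blinded; and adverse-event frequency is tested between arms. Following the text can therefore give a biased adverse-event comparison. A reader might infer that the trial's safety evidence as a whole is compromised. It is not: the primary outcome and the 1-hour secondary outcomes named above are unaffected, and hypertension and bradycardia have numerical thresholds.

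Neither the direction nor the size of any bias can be known from the document. In the illustration, the false-positive rate is 0.14 to 0.33 with 60% v 40% of events counted, and 0.24 to 0.60 with 70% v 40%, over true rates of 20% to 50%. It stays near 0.05 if all events are counted or the filter is equal. Those figures rest on assumed event and attribution rates and on an uncorrected test. The matter should be put right because the safety comparison informs the conclusions and the remedy is inexpensive.

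**What to change.** Reconcile Outcomes, Data collection, Statistical analysis and Safety and adverse events so that they state one rule:

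- Every predefined event under Outcomes and Data collection is recorded over its stated window and compared by arm, whatever its presumed cause.
- Relatedness and expectedness serve reporting purposes only and are presented separately from the comparison. The text says who judges each, preferably someone unaware of allocation.
- Statistical analysis says which list of events the chi-squared comparison covers.

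The cost is a change of wording and longer event listings. If events are currently entered only after passing the definition, some extra recording is needed as well. The article does not show whether that is so, and it should be checked first, because events that were never recorded may be hard to recover later.
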